#### 10.1.1 Reporting of SAE and other safety related events

##### Reporting of AEs

Any AE will be recorded by the PI in the patient's case report file during the assessment visits and if reported by the patient between visits. All AEs will be assessed by the IMC on a weekly basis afterwards.

##### Reporting of SAEs

All SAEs must be reported immediately and within a maximum of 24 h to the sponsor. The sponsor will re-evaluate all reported SAEs in regard to seriousness and causality and, in case of a causal relationship, is given, to expectedness, and inform the site in case of discrepancies to the initial assessment done by the PI.

SAEs resulting in death are reported by the sponsor to the CEC via BASEC within 7 days.

##### Reporting of SUSARs

If a SAE is categorised as SUSAR, it will be reported by the sponsor to the CEC via BASEC and to Swissmedic within 7 days if the event is fatal, or within 15 days (all other SUSARs).

##### Reporting of Safety Signals

All suspected new risks and relevant new aspects of known adverse reactions that require safety-related measures, i.e. so called safety signals, must be reported to the sponsor within 24 h. The sponsor will report the safety signals within 7 days to the CEC via BASEC and to Swissmedic.

##### Reporting and Handling of Pregnancies

Pregnant participants must immediately be withdrawn from the clinical trial. Any pregnancy during the treatment trial and within 28 days after discontinuation of TLN has to be reported to InnoMedica within 24 h. The course and outcome of the pregnancy will be followed up carefully. In case a female partner of a trial participant gets pregnant during the trial, she will be asked by the PI to give her consent in order to collect data regarding the outcome of the mother or the child. Any abnormal outcome regarding the mother or the child should be documented and reported.

##### Periodic reporting of safety

An ASR will be submitted once a year by the sponsor to the CEC and to Swissmedic.

#### 10.1.2 Follow up of (S)AEs

Patients presenting AEs will be followed by the sponsor until the last visit of the patient.

If further support is needed, then the patient will be treated according to the PIs discretion according to clinical practice.

## 11. STATISTICAL METHODS

The present section outlines the statistical principles for the planned analyses of this phase I trial. The analysis will be exploratory and primarily employ descriptive statistical methods. Inferential methods will be used to highlight interesting aspects of the data. Unless otherwise specified statistical tests will be two sided and conducted at the 5% significance level. Corresponding 95%-confidence intervals will be presented and no correction for multiplicity will be applied.

Additional analyses may be defined before DB lock at the end of the treatment phase or during the execution of the planned analysis or after its completion.

### 11.1 Hypothesis

There is not statistical hypothesis for this descriptive phase I trial.

### 11.2 Determination of Sample Size

As the primary objective of this trial is the assessment of safety and tolerability, formal statistical calculations were not used to determine the sample size. The planned number of 3 patients for the dose escalation and 9 for the multiple dosing is considered adequate in the context of the overall trial objectives.

### 11.3 Statistical criteria of termination of trial

There are no statistical stopping rules for this trial. Guidance regarding the discontinuation of the trial subjects, cohorts or the entire trial based on reported AEs are provided in chapter 8.3 **Dose modifications**.

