## **1.6 Internal Monitoring Committee (IMC)**

The IMC is the executive board concerning decisions during the trial (e.g., dose escalation procedure) and consists of the PI, the manager medical affairs, and an external Medical Doctor as an independent medical monitor. The sponsor guarantees the independence of the later as he/she has an important role within the IMC. Every discussion/decision of the IMC will be documented and filed in the trial master file (TMF). Decisions to pursue the trial for each patient will be taken unanimously by the three members. This guarantees that the external member's opinion will have the same value as of the other members.

In principle, the IMC will meet on a weekly basis during the treatment phase in order to evaluate all safety data reported until that timepoint. All data will be verified and SAEs re-assessed before.

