## **1.7 Data Safety Monitoring Board (DSMB)**

The Data Safety Monitoring Board (DSMB) is an advisory board, that is independent from the sponsor and which has no competing interests. Its main objective is to ensure the integrity and safety of participants of the NEON trial by providing unbiased review of raw (not aggregated) clinical trial data. The DSMB consists of 3 independent experts in the field. More details are provided in the trial specific DSMB charter, that serves as guideline of operating principles for DSMB members to oversee patient safety and data quality, to review trial efficacy and progress and to ensure the validity and integrity of the trial on a regular basis.

The DSMB will meet after dose level 5, 10 and 15 during part 1 of the trial, after the maximal suitable dose (MSD) has been defined and after last patient last visit.

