## **2.9 Early termination of the trial**

InnoMedica may terminate the trial prematurely according to certain circumstances, for example:

- ethical concerns,
- insufficient participant recruitment,
- when the safety of the participants is doubtful or at risk, respectively,
- alterations in accepted clinical practice that make the continuation of a clinical trial unwise,
- early evidence of benefit or harm of the experimental intervention

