If a patient drops out for reasons unrelated to the drug treatment, this patient will be replaced. The three MSD are necessary to establish the dose that will be used for the multiple dose administration. This is a design that allows fast escalation with minimal risks for the patients since the dose steps are small, the starting dose is very low and each increment is split in a 1 + 2 pattern. With N=3 we expect to show evidence of common AEs inherent to the TLN formulation. This design (part 1) lacks the assessment of mid-term cumulative effects of the drug at a constant dosage. Therefore, an additional phase (part 2) will be performed to complete the safety profile under constant weekly dosages and provide more insight of the tolerability over 8 repeated doses.

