### 8.3 Dose modifications

Dose modifications are foreseen in cases where a causal relationship to the treatment with TLN cannot be excluded. A causal relationship in this trial is defined as a possible, probable or definite linkage to TLN according to ICH E2A (for more details see section **10. Safety**).

Any grade 4 event with causal relationship to treatment is judged as unacceptable toxicity and will lead to a stop of treatment without resuming the treatment in the affected patient.

Any SAE leads to a treatment stop for the affected patient with the following exception:

- if there is no causal relationship to TLN and the definition for an SAE is fulfilled **uniquely due to an overnight hospital stay (1 night) for an otherwise not severe or serious medical problem**, the patient can continue study participation.

In case of an SAE with no causal relationship to TLN, the patient will be replaced.

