| Probable/definite    | grade 3     | yes                            | stop (for the affected patient but others to continue)                                                                                    |
| Probable/definite    | grade 3     | no                             | Stop for all patients                                                                                                                     |

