#### Part 2 – Dose consolidation:

| Causality            | Intensity   | Resolution until next infusion | Dose repeat                                                                                                                          |
|----------------------|-------------|--------------------------------|--------------------------------------------------------------------------------------------------------------------------------------|
| (unlikely/unrelated) | grade 1 - 3 | yes/no                         | yes                                                                                                                                  |
| Possible             | grade 1     | yes                            | yes                                                                                                                                  |
| Possible             | grade 1     | no                             | yes                                                                                                                                  |
| Possible             | grade 2     | yes                            | yes                                                                                                                                  |
| Possible             | grade 2     | no                             | Delay till resolution (maximum of 3 weeks), then rechallenge at same level, if re-occurrence stop treatment for the affected patient |

|                   |         |        |                                                                     |
|-------------------|---------|--------|---------------------------------------------------------------------|
| Possible          | grade 3 | yes/no | no (stop treatment for the affected patient but others to continue) |
| Probable/definite | grade 1 | yes/no | yes                                                                 |
| Probable/definite | grade 2 | yes    | yes                                                                 |
| Probable/definite | grade 2 | no     | stop (for the affected patient but others to continue)              |
| Probable/definite | grade 3 | yes    | stop (for the affected patient but others to continue)              |
| Probable/definite | grade 3 | no     | stop (for the affected patient but others to continue)              |

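### Section 11.3 points to 8.3 for stopping cohorts or the entire trial, but for Part 2 the rules in 8.3 act only on the affected patient

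*Protocol*

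**What the plan says.** Section 11.3 states that there are no statistical stopping rules. It then adds: "Guidance regarding the discontinuation of the trial subjects, cohorts or the entire trial based on reported AEs are provided in chapter 8.3".

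Section 8.3 has a general text and one decision table per part.

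- General text, both parts: a related grade 4 event "will lead to a stop of treatment without resuming the treatment in the affected patient". An SAE likewise stops treatment for the affected patient, with one exception for an unrelated one-night hospital stay.
- Part 1 table, probable or definite grade 3, not resolved: "Stop for all patients".
- Part 2 table, same causality, grade and resolution status: "stop (for the affected patient but others to continue").

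On the purpose of Part 2, section 6.1.1 says: "This design (part 1) lacks the assessment of mid-term cumulative effects of the drug at a constant dosage". Section 6.1.2 then gives nine further patients the MSD eight times over eight weeks.

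Oversight outside 8.3 includes the IMC, which in principle meets weekly and of which 1.6 says "Decisions to pursue the trial for each patient will be taken unanimously by the three members". The DSMB meets after dose levels 5, 10 and 15, then "after the maximal suitable dose (MSD) has been defined and after last patient last visit" (1.7). The sponsor may end the trial "when the safety of the participants is doubtful or at risk" (2.9).

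**The concern.** A reader who follows 11.3 into 8.3 to learn when Part 2 dosing would be paused for the whole group finds nothing. The one rule above the single patient belongs to Part 1, and Part 2 reverses it for the identical event without giving a reason.

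The direction of the difference is the problem. Part 2 has three times as many patients and is the part meant to show what repeated dosing at a constant level does, in a product with no earlier human data (3.4). A severe event attributed to the drug that does not settle within a week is the kind of signal this part was added to detect. If it occurs, the IMC opens the Part 2 table and reads that the others go on. A decision to hold them would have to be made without support from the table.

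**Working it through.** The point concerns a decision rule, so the plan has no figure to reproduce (11.2 says that no formal sample size calculation was made).

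**Step 1: scope of each rule in 8.3.**

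| Event | Part 1 | Part 2 |
|---|---|---|
| Possible, grade 3 | affected patient | affected patient |
| Probable/definite, grade 2, unresolved | affected patient | affected patient |
| Probable/definite, grade 3, resolved | affected patient | affected patient |
| Probable/definite, grade 3, unresolved | **all patients** | **affected patient; others continue** |
| Related grade 4 (general text) | affected patient; silent on others | affected patient; silent on others |
| SAE (general text) | affected patient; silent on others | affected patient; silent on others |

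Each table has 11 rows. Rows acting on all patients: 1 of 11 in Part 1, 0 of 11 in Part 2. Rules that depend on how many patients are affected: none in either part. One further inversion appears in Part 1: an unresolved grade 3 event can stop everyone, while a related grade 4 event has a stated consequence for one patient only.

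**Step 2: how often a hold would occur in Part 2.** The protocol gives no event rates, so those below are assumptions. Patients are taken as independent, n = 9 (6.1.2).

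Let q be the per-patient risk, over eight infusions, of an event that triggers the hold alone (unresolved probable/definite grade 3, or related grade 4-5). P(hold) = 1 - (1 - q)^9:

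- q = 1%: 1 - 0.99^9 = 0.086
- q = 2%: 1 - 0.98^9 = 0.166
- q = 5%: 1 - 0.95^9 = 0.370

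**Step 3: an optional count trigger.** Let p be the per-patient risk of any related grade 3 or higher event. For two or more affected patients, P = 1 - (1 - p)^9 - 9p(1 - p)^8. For three or more, subtract 36p²(1 - p)^7 as well.

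| p | 2 or more of 9 | 3 or more of 9 |
|---|---|---|
| 5% | 0.071 | 0.008 |
| 10% | 0.225 | 0.053 |
| 20% | 0.564 | 0.262 |
| 30% | 0.804 | 0.537 |

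**Step 4: both triggers together.** With q counted within p, P = 1 - (1 - p)^9 - 9(p - q)(1 - p)^8.

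- p = 5%: q = 1% gives 1 - 0.630 - 9 × 0.04 × 0.663 = 0.13; q = 2% gives 0.19
- p = 10%: q = 1% gives 1 - 0.387 - 9 × 0.09 × 0.430 = 0.26; q = 2% gives 0.30

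**Step 5: what Part 1 already covers.** A patient who reaches level 14 receives 6 + 12 + 60 × (1 + ... + 12) = 4,698 mg. The Part 2 maximum is 8 × 720 = 5,760 mg, so the ratio is 82%. Part 1 therefore does give information on cumulative dose; what it lacks is a constant dose.

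**The case against.** The strongest reply is that Part 2 is closely supervised. The IMC assesses all AEs weekly (1.6, 10.1.1), and its decisions to continue each patient must be unanimous, so one dissenting member, including the external physician, withholds agreement. SAEs and safety signals reach the sponsor within 24 hours, and signals go to the ethics committee and Swissmedic within 7 days (10.1.1). Immediate safety measures and emergency deviations are provided for (2.3, 2.4, 2.10). The DSMB charter and the safety management plan are not shown and may contain ad hoc triggers. All of this stands, and it limits the point to the absence of a rule fixed in advance.

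A second reply is that 11.3 does not promise every level of stopping in every part, and that the tables answer different questions: adding a patient or raising the dose in Part 1, repeating the dose in Part 2. A deliberate difference is possible. However, no reason is given for relaxing the rule, and the stated purpose of Part 2 argues against it.

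Third, a count of affected patients is a design preference, and 11.3 openly says that there are no statistical stopping rules. That is correct, and the count is therefore only an option here.

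Two stronger readings are tempting. A reader might infer that 8.3 orders dosing of the others to continue after a related grade 4 event or an SAE. It does not: the general text is silent about them, and the words on others continuing stand only in table rows for grades 2 and 3. A reader might also estimate the benefit as the infusions that a hold would spare. The documents do not support this. Such a figure assumes that the IMC never acts, and a count of all related grade 3 or higher events includes possible and resolved ones, after which Part 1 too lets the others continue.

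**Conclusion.** The point holds as a gap in the protocol text. For Part 2, the cross-reference in 11.3 leads to rules for the affected patient only, and the one rule that protects the other patients in Part 1 is reversed for the same event. It does not follow that patients would be dosed without oversight, or that harm is likely. The gap is a missing pre-specified cohort-level rule, covered at present by discretion.

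The comparison of the tables needs no assumption. The probabilities rest on assumed event rates and independent patients. They show how often a hold would occur, not how much harm it would prevent, and the protocol offers no basis for quantifying the latter. The conclusion covers the protocol only; the DSMB charter or the safety management plan may already hold part of the answer. The repair is cheap and worth making.

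**What to change.** In the Part 2 table of 8.3, change the unresolved probable/definite grade 3 row: the affected patient stops, and further infusions and new starts are held for the others until an IMC review with ad hoc DSMB advice, for example within 7 days, decides to resume or stop. In the general text of 8.3, apply the same hold to any related grade 4-5 event, in both parts. A count trigger, for example related grade 3 or higher events in two patients, is optional; the sponsor and DSMB should set the number.

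Consequential wording, about one sentence each:

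- 7.3: the hold does not count towards the 3-week delay that leads to withdrawal. Otherwise a long hold would withdraw everyone held.
- 9.3: a visit moved by the hold does not breach the one-day visit window.
- 6.1.3: the hold also covers the prolongation.
- 11.3: state which level of stopping applies in which part.
- 1.7: provide for the ad hoc DSMB review.

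The cost is an amendment, which may need ethics committee and Swissmedic approval (2.10), and a possible pause of about a week. The two mandatory triggers would cause a hold in Part 2 with probability 9%, 17% or 37% at an assumed 1%, 2% or 5% risk. The two-patient count alone would fire with probability 7%, 23%, 56% or 80% at an assumed 5%, 10%, 20% or 30% risk. Combined with the mandatory triggers it fires more often: 13-19% instead of 7%, and 26-30% instead of 23%, if 1-2% of patients have a mandatory trigger. A three-patient count would fire less often (1%, 5%, 26% or 54% alone).

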### 11.4 Planned Analyses

#### 11.4.1 Datasets to be analysed, analysis populations

Three main analysis populations will be employed

- **Safety Analysis Set:** all subjects who received at least part of a dose of the study medication
- **PK Analysis Sets:** subjects from the safety analysis set who provide sufficient data for the key PK evaluations and who do not violate any relevant selection criteria or have protocol violations affecting the assessment of PK.
- **Efficacy Analysis Set:** subjects from the safety analysis set who provide sufficient data for the key efficacy evaluations and who do not violate any relevant selection criteria or have protocol violations affecting efficacy assessments.

For all analyses, subjects will be grouped according to the cohort in which they were treated and/or the dosage they received. The composition of these analysis sets and the dose group or cohort will be finalized before DB lock for the primary who provide sufficient data for the key PK evaluations.

#### 11.4.2 Primary Analysis

Selected safety data, in particular AE reports will be presented periodically by means of descriptive statistics in the Safety Analysis Set.

The primary safety analysis will be performed after completion of the assessments for the last patient. Safety will be tabulated by cohort and where applicable, dose level.

Key data include AE and SAE (incidence, nature, intensity, relationship to study drug), reasons for withdrawal from the study, laboratory data (including Anti-GM1 antibodies), ECG, concomitant medications, physical examination results and vital signs. Adverse events and SAEs will be coded and summarized by body system and preferred term based on the Medical Dictionary for Regulatory Activities (MedDRA).

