## 6. STUDY DESIGN

### 6.1 General study design and justification of design

This trial is a phase I interventional trial consisting of a dose escalation part (1) and a dose consolidation part (2):

- 1- A single ascending dose part in 3 patients for up to 14 weeks plus a follow-up 4 weeks after the last infusion.
- 2- A repeated dose administration part in 9 patients for up to 8 weeks plus a follow-up 4 weeks after the last infusion.
- 3- Optional: The 3 patients from part 1, if they wish, could continue their treatment beyond the planned final assessments for up to 8 weekly TLN infusions.

[figure not shown]

All data will be analysed in a descriptive manner in order to collect first clinical data with this new liposomal formulation of GM1.

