#### 6.1.1 Dose escalation (Part 1)

In this part a group of 3 patients will receive a single weekly dose that will be increased according to the schedule defined. In parallel, meaning that the first patient will receive a dose X on week Y, if the safety assessment is positive (see **Section 8.3 Dose modifications**) then the following week (Y+1) this patient will receive the next dose (X+1), on that week (Y+1) two other patients will receive the same dose X to confirm the safety assessment. *In fine*, every week patient 1 will receive one dose at the same time that patients 2 & 3 receive the preceding dose.

This weekly increase has been elected to allow rapid determination of the MSD and rapidly reach a dose level that will be beneficial for the patients involved in this trial. This is allowed by the fact that GM1 is expected to be safe and no clear AE are foreseen within this dose range. Furthermore, the 1 + 2 pattern allows one week observation of each dose increase in 1 patient before infusing 2 more.

The first dose level starts at 6 mg which will increase to 12 and 60 mg, then increasing by equal steps of 60 mg up to 720 mg. The escalation will be stopped individually according to the decision matrix detailed in the **Section 8.3 Doses modifications**. The three first steps of the dose are purposely low to account for any possible unexpected effects of the formulation.

Throughout the escalation part, all patients will be monitored twice weekly to record AEs and document them. Monitoring will take place once before each TLN infusion (beginning of the week) and a second time by the end of each week (performed by the principal investigator) to collect AE and allow enough time for the IMC to review them and take their decision on the next infusion/dose modification/delay.

At the end of the escalation, the average of the three maximum tolerated doses by the three patients will be defined as MSD for part 2. With this design, we aim to find the highest dose that generates, if any at all, at maximum only transient mild/moderate AEs. At the same time, this will allow to glean information on clinical effect for the planning of a potential phase II study.

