#### Part 1 – Dose Escalation:

The drug will be administrated in a single ascending dose (SAD) as a once weekly i.v. infusion in 3 patients up to 14 dose levels or until unacceptable toxicity appears (see section **6.1.1 Dose escalation** for details on the sequence between patient 1 and 2/3).

The aim of this dose escalating procedure is to define the MSD in terms of the occurrence of AEs dependent on their seriousness, intensity and causality according to the standards and definitions given in this trial protocol (see section **8.3 Doses modifications**).

|               |        |
|---------------|--------|
| Dose level 1  | 6 mg   |
| Dose level 2  | 12 mg  |
| Dose level 3  | 60 mg  |
| Dose level 4  | 120 mg |
| Dose level 5  | 180 mg |
| Dose level 6  | 240 mg |
| Dose level 7  | 300 mg |
| Dose level 8  | 360 mg |
| Dose level 9  | 420 mg |
| Dose level 10 | 480 mg |
| Dose level 11 | 540 mg |
| Dose level 12 | 600 mg |
| Dose level 13 | 660 mg |
| Dose level 14 | 720 mg |

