9.3.6 Visit 31: Follow-up (28 days after TLN infusion)

- Clinical assessment (including physical medical and neurological exam, height and weight).
- Vital signs
- Full lab test
- MDS-UPDRS
- LEDD
- AE recording

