## 10. SAFETY (DRUG STUDY)

As sponsor of this trial, InnoMedica has established a framework of quality assurance which encompasses responsibilities and documents (e.g., SOPs) which fully cover safety aspects. During the entire duration of the trial, all AEs and all serious adverse events (SAEs) are collected, fully investigated and documented in source documents and case report forms (CRFs). Trial duration encompassed the time from when the participant signs the informed consent until the last protocol-specific procedure has been completed, including a safety follow-up period of 28 days. The SMP provides detailed information.

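### Adverse event incidence by dose level and cohort takes no account of time at risk: about 7 days at an intermediate Part 1 level against 28 at each patient's last, and 119 days per Part 1 course against 77 in Part 2

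*Protocol*

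**What the plan says.** Protocol section 11.4.2 sets out the primary safety analysis. Its content is given as "Key data include AE and SAE (incidence, nature, intensity, relationship to study drug" and so on, and its layout as "Safety will be tabulated by cohort and where applicable, dose level". Section 11.4.1 adds that "subjects will be grouped according to the cohort in which they were treated and/or the dosage they received". Neither section gives a time at risk, a rule for assigning an event to a dose, or a window after an infusion.

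The schedule comes from other sections. Part 1 is given "as a once weekly i.v. infusion in 3 patients up to 14 dose levels or until unacceptable toxicity appears" (section 8.1.1), and under section 6.1.1 "every week patient 1 will receive one dose at the same time that patients 2 & 3 receive the preceding dose". A patient therefore has one infusion per level, a week apart. Section 6.1 describes Part 1 as "A single ascending dose part in 3 patients for up to 14 weeks plus a follow-up 4 weeks after the last infusion", and AE recording is listed at that follow-up visit (section 9.3.6). Section 10 collects AEs over the whole trial, "including a safety follow-up period of 28 days". Part 2 gives eight weekly infusions on days 1 to 50 with the same 28-day follow-up (sections 9.3.9 to 9.3.13).

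**The concern.** Incidence compares fairly across columns only if the columns have similar observation time. Here they do not, and the difference comes from the planned schedule itself, without any extension data. The longest observation falls on the last level each patient receives. Ordinary background events can therefore produce a step up at that level with no drug effect. For a patient who stops early, the extra events would attach to the stopping dose and could look like confirmation of toxicity.

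There is no control group, so the dose gradient is the main internal comparison for safety, and section 4.1 makes a recommended phase II dose part of the overall objective. With three patients per level, one or two additional events change the picture. The grouping rule in section 11.4.1 does not help, because it groups subjects and one Part 1 subject may receive 14 dosages.

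**Working it through.** The protocol states no AE rate, observation ratio or sample size calculation, so there is no figure of its own to reproduce. Background rates below are assumptions, shown as a range.

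**Observation time from the schedule (no delay, no continuation)**

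- Intermediate Part 1 level: infusion to next weekly infusion = 7 days.
- Last Part 1 level: last infusion to follow-up = 28 days.
- Full Part 1 course: infusions on days 1, 8, …, 92 and follow-up on day 120, so 13 × 7 + 28 = 119 days.
- Part 2 course: infusions on days 1 to 50 and follow-up on day 78, so 7 × 7 + 28 = 77 days.
- Share of Part 1 time after the last infusion: 28/119 = 23.5%, against 1/14 = 7.1% of infusions.

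**Expected event counts at a constant rate, each AE assigned to the most recent infusion**

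- Last against intermediate level: 28/7 = 4.0. Applying the ±1 day visit window of section 9.3 to each interval gives 27/8 = 3.4 to 29/6 = 4.8.
- Part 1 against Part 2, per patient: 119/77 = 1.55. This needs no rule for assigning events to doses.

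**Probability that a patient has at least one AE**

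The formula is 1 − exp(−days × rate).

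| Assumed rate | Intermediate, 7 days | Last, 28 days | Ratio | Part 1, 119 days | Part 2, 77 days | Ratio |
|---|---|---|---|---|---|---|
| 1 per 30 patient-days | 20.8% | 60.7% | 2.9 | 98.1% | 92.3% | 1.06 |
| 1 per 60 patient-days | 11.0% | 37.3% | 3.4 | 86.2% | 72.3% | 1.19 |
| 1 per 90 patient-days | 7.5% | 26.7% | 3.6 | 73.3% | 57.5% | 1.28 |

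The incidence ratio by dose stays below 4 and falls as the rate rises. At one AE per patient-week it is (1 − exp(−4))/(1 − exp(−1)) = 0.982/0.632 = 1.55.

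**What moves the ratio**

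- *Delay:* section 8.3 allows a delay of up to 3 weeks and then a rechallenge at the same level. That level then has about 7 + 21 + 7 = 35 days, and the ratio becomes 28/35 = 0.8, which reverses the gap.
- *Continuation:* section 6.1.3 allows up to 8 further weekly infusions at the patient's own maximum or at level 14, and section 9.1 appears to add these data to Part 1. Pooled by dose level, the last level would have 28 + 49 + 28 = 105 days, a ratio of 105/7 = 15.

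**After correction**

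With events per patient-week, or an equal 7-day window after each infusion, the no-effect ratio is 1.0 at every level. The time still adds up: 14 × 7 = 98 on-dose days plus 21 later days = 119.

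**The case against.** The strongest reply is that this belongs in the statistical analysis plan. The protocol never says that follow-up days count toward the last dose, dose-level tables are promised only where applicable, and group composition is to be finalised before database lock. Attribution windows and exposure-adjusted rates are commonly set in the analysis plan, which is not at hand. This stands in part: assignment to the most recent infusion is the natural reading, not a stated rule, and the protocol commits no arithmetic error. What remains is that section 11.4.2 does fix the measure and the layout, and the cohort table is unconditional. An analysis plan that follows the text literally would carry the imbalance forward.

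Second, scheduled ascertainment is not 4 to 1. An intermediate level is followed by two AE visits (the mid-week assessment and the next infusion). The last infusion is also followed by two (day +7 and day +28). This weakens strict proportionality to days. It does not remove it, because section 9.2.1 asks patients to report effects between visits and records time of onset. Part 1 is also monitored twice weekly and Part 2 weekly, so a rate per patient-week does not make the cohorts fully comparable.

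Third, the two parts differ by design in dose and number of infusions, and no between-cohort test is planned. That is right, but side-by-side columns will still be read against each other.

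A reader might also infer that the imbalance distorts the dose carried into Part 2. The documents do not support that. The Part 2 dose is the average of the three patients' maximum doses, reached through the event-by-event matrix in section 8.3. The primary safety analysis runs only after the last patient has finished.

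**Conclusion.** The point holds as a weakness in how the primary outcome is displayed. Under assignment to the most recent infusion and a constant background rate, the last level shows about 4 times the expected event count, and about 2.9 to 3.6 times the patient incidence at one AE per 30 to 90 patient-days. Part 1 shows 1.55 times the expected count per patient of Part 2.

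Three stronger readings should be set aside:

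- Four is a ratio of event counts, not of patient incidence.
- Four is not a ceiling. Delay with rechallenge can reverse the gap and pooled continuation data can enlarge it.
- The long window belongs to each patient's last level, which is level 14 only for those who complete the escalation.

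The consequence is confined to how the dose gradient and the phase II recommendation are read. With three patients per level, any comparison by dose remains descriptive.

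**What to change.** Add to section 11.4.2, or carry into the analysis plan:

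- Assign each AE to the most recent infusion by onset date.
- By dose level and by cohort, report patient-days at risk and events per patient-week beside the number of patients with an event.
- Show events with onset more than 7 days after an infusion (post-treatment follow-up or a treatment delay) in a separate column that still identifies the last dose received. Give that column its own patient-days.
- Show events during optional continuation in a further separate column, also with the dose identified.

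Seven days matches the dosing interval and is 168/30 = 5.6 of the projected 30-hour half-lives (section 6.1.2). It should not serve as a hard cut-off in the only display, since delayed reactions must stay visible and linked to the dose.

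The cost is a little more table work, and late events appear apart from the on-dose column. Onset times are already collected under section 9.2.1, so no visit, data item or clinical rule changes.
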